### **Respiratory infections symptoms diary (III)**

Symptom diary was built accordingly to the previously published respiratory infection assessment and after a pilot study to search for comprehensibility and adaptability to the population age [45, 46]. It was subdivided in five main symptoms categories: general symptoms (shivering, muscle pain, tiredness, chest pain, dyspnea), nasal symptoms (runny nose, obstructed nose, sneezing, nose itch), eye symptoms (itching eyes), throat symptoms (sore throat, itching throat, cough and hoarseness) and ear symptoms (ear pain) and body temperature. Temperature was registered, if the absolute value was above 37.5°C. Each symptom would be classified accordingly to the severity in mild, moderate or severe by the participant.

Respiratory infections were defined accordingly to symptoms assembly and period of time. Duration of respiratory infection was calculated accordingly to the symptoms that were correspondent to infection episode duration. Severity of the respiratory infections was classified as mild, moderate or severe, based in the type of symptoms and if they affected general health state of the individual.

Probable respiratory infection was defined by obtaining in at least three consecutive days, one of the four different settings:

- moderate or severe symptoms in two of five symptom categories (excluding the allergic symptoms namely nasal or ocular pruritus);
- mild/moderate symptoms in more than 3 symptom categories
- cough associated to at least 3 symptoms of 2 different symptom categories
- fever with other respiratory symptom.

Severity of respiratory infection was classified in: severe (participant had a systemic infection and/or severe local symptoms); moderate (mild systemic symptoms with moderate local symptoms) and mild (mild to moderate local symptoms).

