Exercise testing (IV), namely maximal symptom-limited exercise testing is a relatively safe procedure, especially in otherwise healthy individuals. Fatality risk is related to medical complications to the underlying disease and the rate of death per patients during exercise testing is 2 to 5 per 100.000[75]. Strict contra-indications will be followed. A licensed physician and an cardio-respiratory technician will observe the participant during exercise and the recovery period and watch for undue stress (e.g., severe wheezing, chest pain, lack of coordination) or adverse signs (e.g., ECG abnormalities, falling blood pressure, decrease in O2 saturation), if it occurs the test will be immediately stopped and any adverse event treated. A resuscitation cart will be immediately available. The population tested in this study will be young and otherwise healthy without know disease, only chronic co-morbidity will be asthma and obesity. Exercise induced bronchoconstriction is assessed by exercise challenge and it is a recommended and widely used method to evaluate asthma patients. Furthermore these population will be under controlled asthma. If any adverse event occurs, namely bronchoconstriction it will be immediately reversed with bronchodilation.

Exercise intervention in the elderly population (III), was already submitted and accepted by the ethical commission (**Attachment 6**). Moderate exercise program will be performed and adapted to each elderly participant, co-morbidities and difficulties and physical condition and anaerobic resistance for exercise strength will be evaluated previously to the training by resistance maximum. Exercise will then be adapted to each individual condition and progressively increased at each participant rhythm. The exercise will be guided by sports professors trained in exercise teaching and monitoring. Potential adverse conditions can occur, namely muscle and body ache which will be self-limited and prevented by this progressive adaptation to exercise. All elderly will have an individual insurance if any adverse event occurs, namely falls during training or any unavoidable accident.

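### Study III: training-related muscle ache can tip a nasal, throat or ear complaint into a probable infection more often in the training arm, and the itch exclusion is written into only one of the four settings

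*Protocol*

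**What the plan says.** Protocol 4.2.1, under the symptoms diary for Study III, gives the case definition: "Probable respiratory infection was defined by obtaining in at least three consecutive days, one of the four different settings". The settings are:

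1. "moderate or severe symptoms in two of five symptom categories (excluding the allergic symptoms namely nasal or ocular pruritus"
2. "mild/moderate symptoms in more than 3 symptom categories"
3. "cough associated to at least 3 symptoms of 2 different symptom categories"
4. "fever with other respiratory symptom"

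The first of the five categories is "general symptoms (shivering, muscle pain, tiredness, chest pain, dyspnea". The eye category has one item, itching, and the ear category has one item, ear pain.

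Section 4.1.3 describes a non-randomised, unblinded comparison. One group does aerobic and resistance training three times a week for 36 weeks, and the control group does not. The same section says that itch items were recorded so that allergy could be excluded when the diary is evaluated, and that symptoms present on all or most days of the study were dropped.

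On the effects of training, the Safety section says: "Potential adverse conditions can occur, namely muscle and body ache which will be self-limited and prevented by this progressive adaptation to exercise".

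The definitions for Studies I and II differ. Sections 4.1.1 and 4.2.1 (questionnaire) require at least one of four cold-specific nasal or throat symptoms. Study III has no such requirement in settings 1 to 3 beyond the cough in setting 3.

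**The concern.** The outcome of Study III is whether a participant had a respiratory infection, and 4.3.2 bases the comparison on the relative risk between arms. If the intervention produces a symptom that counts towards the outcome, the same nasal or throat complaint can be scored differently according to arm. That is differential misclassification caused by the treatment. The covariates listed in 4.3.2 for the elderly model (sex, age, BMI, respiratory history, diabetes, smoking, influenza vaccination, previous exercise) are baseline characteristics and cannot remove it. The diary is self-reported and participants know their arm.

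A second fault lies in the same list. The itch exclusion appears only in setting 1, although 4.1.3 states it as a purpose of the whole diary.

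**Working it through.** **The plan's own figure.** The protocol gives no error rate for the case definition. Its only related figure is the 30% power in 4.3.2, for 48% against 30% with 40 per group. Two-sided at 0.05 with continuity correction, power = Φ((0.18 − 1/40 − 1.96 × 0.1091)/0.1072) = Φ(−0.548) = 29.2%. Fisher's exact test gives 30.1%. The figure reproduces and does not depend on the point made here. The 30% and 48% are reused below as inputs only.

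**Can general symptoms alone qualify?** Setting 1 needs a second category, setting 2 needs at least four, setting 3 needs cough, and setting 4 needs fever plus a respiratory symptom. All severity combinations of the five general symptoms were enumerated, and none met any setting.

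**Can they tip a pattern that otherwise fails?** Each pattern is held for three days, without fever:

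| Local complaint | Alone | With general symptoms added |
|---|---|---|
| Moderate nasal obstruction | none met | moderate muscle pain: setting 1 |
| Moderate cough | none met | moderate muscle pain: setting 1 |
| Mild cough and sore throat | none met | mild muscle pain and tiredness: setting 3 |
| Mild nasal, throat and ear symptoms | none met | mild muscle pain: setting 2 |

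In the third row, muscle pain without tiredness is enough if the cough may itself be one of the three symptoms; the text leaves this open. Setting 1 is also met by moderate muscle pain with moderate ear pain, with no nasal or throat symptom at all.

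**Does the most-days rule remove the ache?** The study lasts 36 × 7 = 252 days and an episode needs three. Ache on three days is 3/252 = 1.2% of the period, so the rule removes chronic complaints and leaves intermittent ache.

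**Setting 2 and itch.** More than three of five categories means at least four. General, nasal and throat make three, so the fourth must be ear pain or eye itch. A mild runny nose, sore throat and tiredness (no cough, no fever) meets no setting. Adding itchy eyes meets setting 2 as written. If itch is excluded throughout, the eye category is empty, four categories remain, and more than three means all four, so ear pain becomes compulsory.

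**Illustration of size (assumed inputs).** Let f be the share of truly uninfected participants who are scored as infected. With a true risk of 30% in both arms, observed risk = 0.30 + 0.70 × f. With f = 0 in controls:

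| f, training arm | Observed risk, training arm | RR if truly 1.00 | RR if truly 0.30/0.48 = 0.63 |
|---|---|---|---|
| 5% | 33.5% | 1.12 | 0.70 |
| 10% | 37.0% | 1.23 | 0.77 |
| 20% | 44.0% | 1.47 | 0.92 |
| 30% | 51.0% | 1.70 | 1.06 |

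The last column assumes 30% in trained participants and 48% in controls. That is the direction of the reduced incidence reported in the Rationale; the power paragraph in 4.3.2 states the two figures the other way round. Zero in controls is the extreme case. With f = 20% in training and 10% in controls, the RR for a true null is 0.44/0.37 = 1.19. With equal f it is 1.00. Section 4.1.3 reports 38 participants selected; with an equal split (assumed), one misclassified person moves an arm by 1/19 = 5.3 points.

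**The case against.** Several points on the other side stand. Soreness cannot qualify without another complaint. The Safety section says that ache can occur and is prevented by gradual adaptation, and it does not mention tiredness. Controls came largely from nursing homes and day-care centres, and osteo-articular disease is a recorded co-morbidity, so they can report muscle pain and tiredness too. Counting systemic symptoms follows the source instruments: the questionnaire in 4.2.1 includes feeling tired, 4.1.1 adds body ache to it, and the cold score in 4.2.1 includes malaise. Removing these items gives up some sensitivity. Section 4.1.3 can be read as excluding itch from the whole diary, and the setting 2 fault applies to both arms.

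Replacing the primary definition would also be hard to defend. Milestones place the end of the Study III analysis at month 18, about February 2012 from the September 2010 start, and the document is dated 10 December 2012.

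These points limit the claim without removing it. Bias needs only an excess of ache in the training arm, and nothing in the definition discounts it. Reading the itch exclusion into setting 2 leaves that setting dependent on ear pain.

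**Conclusion.** The point holds as a threshold effect. General symptoms count in settings 1 to 3, one arm has a stated possible source of muscle ache, and no rule separates that ache from infection. The likely result is extra probable infections in the training arm, which works against showing a benefit. This assumes that training produces more ache than controls have, and that some of it coincides for three days with a local complaint.

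The size is unknown. The relative risks above show sensitivity to assumed inputs and are not estimates. A reader might infer that training by itself creates infections, that only the exercise arm is affected, or that the protocol expects training to cause tiredness. The documents support none of these: no general-only pattern qualifies, controls can ache, and tiredness is not named as an effect of training.

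The itch fault is separate. It is a drafting error that affects both arms and needs correcting in its own right.

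**What to change.** - Keep the stated definition as primary, but write the nasal and ocular itch exclusion into all four settings. Restate setting 2 as a number out of the four categories that remain (general, nasal, throat, ear), and say whether the cough in setting 3 counts among its three symptoms.
- Add a sensitivity analysis on the existing diaries, scored by someone blind to arm. Drop muscle pain and tiredness from the category and symptom tallies, and require at least one non-itch nasal or throat symptom in every setting, in line with the cold-symptom requirement for Studies I and II.
- Report both results with the number of episodes reclassified per arm. If they differ, limit the conclusion about training accordingly. If the analysis had already been run, say that these changes came afterwards.

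The cost is some extra scoring and no new data. The sensitivity analysis will miss some infections with mainly systemic symptoms, and that loss need not be equal between arms.

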## **4.2.2. Health state and quality of life measurements (I,II)**

### **Health state and quality of life questionnaire (MOS SF-36v2)**

At the third day of illness in the respiratory infection questionnaire validation it will be also filled in a validated questionnaire in Portuguese, MOS SF-36 (**Attachment2**), of health state. Quality of life was assessed using the SF-36, a self administered, widely used questionnaire, and validated to quantify subjective reports of health in terms of functional status, emotional status, and general well being[41, 42]. This generic instrument is composed of 36 questions, distributed

into eight different dimensions of health: physical function, role limitations related to role physical, bodily pain, general health perception, vitality, social functioning, role limitations due to emotional problems, and mental health. Each dimension is reported on a scale from 0 to 100 with a higher score reflecting better quality of life[41, 42].

### **Anxiety questionnaire**

The Zung self-rating anxiety scale is a questionnaire aimed to evaluate a state of anxiety more than a anxious personality[47]. It has been validated in portuguese and is composed by 20 items that explore affective (5 items) and somatic (15 items) aspects of anxiety, on a 4-level scale[47, 48]. The total point score can range from 20 to 80. A high score indicate a high degree of anxiety. (**Attachment 4**).

### **Sleep and sleep quality questionnaire**

To understand and evaluate sleep quality a questionnaire will be applied, asking sleep habits and sleep quality, both addressed by the Pittsburgh Sleep Quality Index. This is a self-rated validated questionnaire that assesses sleep quality and sleep disturbances over a 1- month time interval. A score >5 is used to define a 'poor sleeper'. (**Attachment 3**)

## **4.2.3. Nutritional Assessment (II, VI)**

### **Anthropometric measures (II,IV)**

Anthropometric measures will include weight, height and specific measures to determine body composition, namely a triceps skinfold thickness and medial calf skinfold thickness.

Weight will be measured to the nearest 0,1 kilogram and height will be measured to the nearest 0,5 centimeters. Subjects will be lightly clothed and bare-footed.

After height and weight, it will be calculated body mass index (BMI) - weight (kilograms) divided by square of height (meters).

Individuals will be classified according to World Health Organization (WHO) classifications: normal weight, 18.5 to 24.9 kg/m^2; overweight, 25.0 to 29.9 kg/m^2; obesity, 30.0 kg/m^2 or plus.

Skinfold thickness measurement will be taken using a slim guide skinfold calipers and according to procedures described by International Society for the Advancement of Kinanthropometry (ISAK)[49]. Three measurements will be taken, at each site (+/- 0,1 mm). Percentage body fat will be calculated using prediction equations (Males: % body fat = 0,735 \* (triceps + calf) + 1.0 / Females: % body fat = 0,610 \* (t+c) + 5.1), as previously published [50].

Waist circumference will be measured according to procedures described on ISAK[49]. Individuals will be classified in abdominal overweight or obese, according to the following sex-specific cut-offs: females - abdominal overweight 80 - 88 cm, abdominal obesity 88 cm or plus; males - abdominal overweight 94 - 102 cm, abdominal obesity 102 cm or plus[51].

### **Dietary Reports (II, IV)**

Dietary intake will be assessed by a repeated 24-hour recall. Participants will be asked to provide detailed information about their dietary intake, through a 24-hour dietary recall method. This method will be conducted in four steps: first, individuals will be asked to inform the interviewer about all foods and beverages they've consumed in the previous 24 hours; second it will be questioned for foods that are documented as being frequently forgotten; third, individuals will be asked about the time and occasion at which foods were consumed; finally, the interviewer will ask questions about food description and amounts.

Participants of study IV, will provide their reports on the first and second meetings.

#### **4.2.4. Airway Inflammation (III)**

Sputum collection and analysis will be performed as described previously in literature [52]. Patients will perform previously bronchodilation with salbutamol followed by a protocol of inhalation of hypertonic saline (5%NaCl) generated by an ultrasonic nebulizer during 5 min periods for 20 min. Sputum will then be obtained. After the sample is collected it will be selected in a Petri dish, and the selected sample treated with dithiothreitol (Sputolysin; Calbiochem Corporation, San Diego, CA, USA). The suspension will be centrifuged and the cell pellet re-suspended. Cytospins will be prepared and stained using May-Grünwald/Giemsa. Differential cell counts will be made by counting a minimum of 500 nonsquamous cells. Sputum eosinophilia will be defined as a sputum differential of eosinophil count over 4%.

Metabolomics is the study of small molecules (0,1 kDa) generated from cellular metabolic activity and it seems to be a potential biomarker for airway inflammation[33]. Exhaled breath has potential to be a matrix with relevant metabolomic information to characterize asthma[34, 53]. Comprehensive two-dimensional gas chromatography–time of flight mass spectrometry (GC ×GC–ToFMS) has been used to on exhaled breath in patients with asthma and a pattern of six compounds belonging to the alkanes were found that characterized the asthmatic population: nonane, 2,2,4,6,6-pentamethylheptane, decane, 3,6-dimethyldecane, dodecane, and tetradecane. This profile can be useful for distinguishing patients with asthma from other different inflammatory airway disease and possibly new profiles can be withdrawn from this technique, namely characterizing an illness prone profile [34, 53]. The breath sampling will be obtained as previously published [34, 53]. Briefly, in a previously clean 1 L Tedlar® bags and after washing the mouth with water will exhale deeply into the Tedlar® bag previously holding their breath for 5 seconds. All bags will be analyzed for a maximum of 6 h after the collection [34, 53]. This analysis can also be performed in exhaled air condensate, this is obtained accordingly to the previous published guidelines. Extraction/concentration will be done with HS-SPME methodology to coating fiber, this will then be introduced into the GCx GC–ToFMS, which consists of an Agilent GC 7890A gas chromatograph, with a dual stage jet cryogenic modulator. Detection will then be performed by a high-speed ToF mass spectrometer. In order

to identify the different compounds, the mass spectrum of each compound detected will be compared to those in mass spectral libraries databases[34, 53].

#### **4.2.5. Lung function and airway responsiveness (III, IV,V)**

Spirometry will be carried out according to the American Thoracic Society criteria[54]. Lung function measurements will be repeated 15 minutes after 400 µg of salbutamol in aerochamber to assess reversibility.

Non-specific bronchial hyper-responsiveness will be measured by methacholine challenge, according to the previous published guidelines. Methacholine will be delivered by inspiration triggered by a dosimeter, five-breath will be needed and PD20 (provocative dose causing a 22% fall in forced expiratory volume in one second (FEV1)) determined.

The capsaicin challenge will be performed accordingly to the previous guidelines [55]. The procedure will be performed in a ventilated area. Fresh dilutions of capsaicin solution (capsaicin in powder (30.54 mg) dissolved in 1 ml of Tween 80, 1 ml of ethanol and 8 ml of normal saline) are performed with physiological saline in the laboratory, previous to the challenge and stored at 4°C. Dilutions of 0.49, 0.98, 1.95, 3.91, 7.81, 15.63, 31.25, 62.5, 125, 250 and 500 µM are prepared. Three ml of each solution are provided by nebulizer through a dosimeter. Subjects perform a baseline spirometry and then start the protocol: inhaling a control solution of normal saline followed by progressively increasing concentrations of capsaicin solutions at 2 minutes intervals. A breath-activated nebulizer controlled by a dosimeter (Optineb®, Air Liquide), set to nebulize for 0.9s will be used. Subjects are asked to cough freely and the concentrations inducing 2 and 5 coughs during the 30 seconds period after capsaicin administration will be registered. The test is finished when 5 coughs are elicited or when the maximal dose (500 µM) is achieved. At the end of the challenge, a new spirometry is performed.

#### **4.2.6. Allergic and inflammatory systemic markers (III, IV, V)**

Skin prick tests will be carried out in accordance international guidelines with a standard battery of commercial extracts for common aeroallergens[56, 57]. Histamine dihydrochloride (10mg/ml) and diluent will be as used as positive and negative controls, respectively. The tested extracts will be stored at +2 to +8°C when not in use. A small drop of each testing solution will be placed on the volar forearm surface of the patient arm and then pressed against the skin in the centre of the allergen drop for at least 1 s without causing bleeding. Results will be recorded after 15 min. The largest and perpendicular diameter of the wheal for each of the allergens is measured and the following value calculated: largest + perpendicular diameter/2. A subject is defined as atopic in the presence of at least one positive result (regarded if the value calculated was ≥3 mm and controls showed adequate reactions) [56, 57].

Inflammatory systemic markers, namely urine metabolome (study II), will be performed by the same methodology already described in the metabolomic analysis of the exhaled breath condensate on point 4.2.4.

#### **4.2.7. Parasympathetic activity measure (III,IV)**

Pupillary measurements will be taken with a portable infrared PLR-200™ Pupillometer (NeuroOptics Inc, CA, USA). This comprises in two major parts, a hand-held optical unit and an electronic board. The subjects will be asked to spend at least 15 min in a room to allow their eyes to adjust to the low lighting levels before any measurements are undertaken on their pupils. Each subject will sit upright on a chair and the measurements are performed by the operator by resting the pupillometer optical unit against the subject's face. Two pairs of infrared-emitting diodes of an 880-nm wavelength (programmed to adjust intensity automatically for papillary pigmentation and ambient light) will illuminate the eye. The measurement takes about 3 seconds. At the end of the measurement cycle, a graph of the pupil diameters as a function of time will appear on the host screen. Five pupil light response curves will be recorded. The following parameters will be calculated: initial diameter (Init Dia), minimum diameter (Min Dia), final diameter (Final Dia), time to minimum diameter (TTM), reflex amplitude (RA= Init Dia\_Min Dia), constriction velocity (CV), reflex amplitude as percentage of initial diameter (%RRA), maximum constriction velocity (Max CV), time to maximum constriction velocity (TM MCV), maximum redilation velocity (Max RV), time to maximum redilation velocity (TM MRV), relative redilation residue as percentage (%RRR = Init Dia\_Final Dia/Init Dia\_Min Dia), and time at which pupil has re-dilated 75% of the reflex amplitude (TM 75%).

Heart rate after 15 min rest will be measured , during the procedure verbal instructions and a practice period of paced breathing will be provided.

